# Acupuncture on GB34 for immediate analgesia and regulating pain-related anxiety for patients with biliary colic: a protocol of randomized controlled trial

**DOI:** 10.1186/s12906-023-04030-8

**Published:** 2023-07-07

**Keywords:** Biliary colic, Acupuncture, Randomized controlled trial, Protocol

## Abstract

**Background:**

Biliary colic (BC) is a frequent hepatobiliary disorder encountered in emergency departments. Acupuncture may be effective as an alternative and complementary medicine for BC. Nonetheless, rigorous trials investigating its efficacy are lacking. Therefore, the aim of this study protocol is to determine whether acupuncture provides immediate relief of pain and associated symptoms in BC patients.

**Method:**

Eighty-six participants who aged from 18 to 60 years with BC will be recruited in the First People's Hospital of Longquanyi District, Chengdu (West China Longquan Hospital Sichuan University). All participants will be allocated into two treatment groups including acupuncture group and sham acupuncture group using a 1:1 ratio. Each group will only receive a single 30-min needle treatment while waiting for their test results after completing the routine examination for BC. The primary outcome of the study is to assess the change in pain intensity after the 30-min acupuncture treatment. The secondary outcomes of the study include the change in pain intensity at various time points, the degree of gastrointestinal symptoms at different time points, the level of anxiety experienced during pain episodes at different time points, the score of Pain Anxiety Symptoms Scale-20 (PASS-20), the score of Fear of Pain Questionnaire-III (FPQ-III), and the score of Pain Catastrophizing Scale (PCS), among others.

**Discussion:**

The results of this research will provide substantial evidence regarding the efficacy of acupuncture in alleviating symptoms associated with BC.

**Trial registration:**

ClinicalTrials.gov, ChiCTR2300070661. Registered on 19 April 2023.

**Supplementary Information:**

The online version contains supplementary material available at 10.1186/s12906-023-04030-8.

## Background

Biliary Colic (BC) is a symptom of an acute attack of gallstones. The prevalence of gallstones has been displayed to be 10%-20% patients in worldwide. Furthermore, more than 20% of patients with gallstones will develop BC symptom [1]. It is estimated that complications occur in approximately 1%–3% of patients with symptomatic gallstones annually [2]. BC is characterized by persistent pain in the upper part of the abdomen, back, or right shoulder, as well as nausea and vomiting, which are caused by the contraction of the gallbladder pushing bile across the blockage [3].

The affective component of pain includes feelings of distress, sadness, anxiety, and depression in response to noxious stimuli [4]. Depression and anxiety have been linked to prolonged duration of acute pain [5]. Likewise, BC, being an acute pain, may be clinically accompanied by emotional symptoms such as anxiety and depression. Studies on pain-induced anxiety have demonstrated that acute pain intensity is positively correlated with anxiety status [6, 7]. Literature on pain-induced depression has suggested that acute pain may contribute to depressive symptoms following surgery [8].

An evidence-based clinical practice guideline for the remission of BC has recommended non-steroidal anti-inflammatory drugs (such as diclofenac and indomethacin), spasmolytics (such as butylscopolamine), opioids (such as buprenorphine), and cholecystectomy (within 24 h after the diagnosis of biliary colic) [9–11]. However, pharmacological treatments may have side effects, including serious gastrointestinal complications, cardiovascular events, hypersensitivity, itch, nausea, and vomiting, among others [12–17]. Additionally, cholecystectomy may be accompanied with post cholecystectomy syndrome [18, 19]. Thus, complementary alternative therapy is considered essential to improve BC symptoms.

Acupuncture, as part of traditional Chinese medicine, potentially relieves the pain-related disorders [20–22]. Some clinical studies have proved that acupuncture can alleviate pain-related symptoms of BC [23, 24]. Moreover, our team found that acupuncture for BC is effective through the imaging mechanism of acupuncture at GB34 in the early stage. However, the research has mainly focused on the mechanism of pain, and the sample size was relatively small, despite patients with BC often experiencing emotional problems [25, 26]. Therefore, thus far, it is unclear whether acupuncture has analgesic effects on BC owing to the methodological limitations in control groups, randomization, and blinding, among other factors.

Hence, a randomized, sham-controlled trial will be conducted to assess the potential of acupuncture in improving pain and related symptoms of BC.

## Methods/design

### Study design

The single center, sham-controlled, blinded, randomized trial of acupuncture treatment for BC will be executed in the First People's Hospital of Longquanyi District of Chengdu (West China Longquan Hospital Sichuan University) from May 2023 to July 2024. The protocol of trial has been approved by the Affiliated Hospital of Chengdu University of Traditional Chinese Medicine (No. 2023KL-008). And it has been registered with an identifier (ChiCTR2300070661) at ClinicalTrials.gov (https://www.chictr.org.cn/). The trial will be performed in accordance with the Standard Protocol Items: Recommendations for Interventional Trials (SPIRIT) checklist [27]. Moreover, informed consent will be obtained from all patients prior to beginning the trial. All BC patients will accept acupuncture treatment while patients are waiting for the test results after completing routine examinations. If patients with BC continue to experience pain after acupuncture treatment, conventional treatment will be administered, and the pain relief time will be recorded. The study flow chart is shown in Fig. 1, and the study time schedule is presented in Table 1.

**Fig. 1 Fig1:**
[figure not shown]
Trial flow chart

**Table 1 Tab1:**
[figure not shown]
Trial processes chart

The use of rescue analgesia will be recorded 10 min after the completion of acupuncture, As the specific time for each subject to use the analgesic may vary, "…" will be used to indicate the time

### Participants

Eighty-six patients with BC will be recruited from the emergency department of the First People's Hospital of Longquanyi District of Chengdu (West China Longquan Hospital Sichuan University). All patients will be screened by Specialists and acupuncturists according to the diagnostic criteria from the Recommendations for EASL clinical practice guidelines on the prevention, diagnosis and therapy of gallstones (2016) [9].

### Inclusion criteria

Participants who meet the following inclusion criteria will be eligible for the study: (i) those who meet the diagnostic criteria; (ii) mild tenderness in the right upper quadrant, negative or positive Murphy's sign; (iii) a numerical rating scale (NRS) score of ≥ 3 points; (iv) BC patients aged between 18 to 60 years, without any gender restrictions; (v) gallbladder stones demonstrated by radiology or ultrasonography; (vi) no history of acupuncture treatment within the past month; (vii) not participating in any other clinical studies; and (viii) willing to voluntarily sign the informed consent form.

### Exclusion criteria

Participants who meet the following exclusion criteria will be excluded from the study: (i) a history of jaundice; (ii) presence of bile duct stones, acute cholecystitis, acute suppurative cholecystitis, gangrenous cholecystitis, incarcerated cholecystitis, gallbladder perforation with diffuse peritonitis, or BC complicated with acute pancreatitis; (iii) administration of analgesics such as antispasmodic, non-steroidal anti-inflammatory drugs, or choleretic before acupuncture; (iv) presence of serious complications or primary diseases involving the brain, cardiovascular, liver, kidney, endocrine, or hematopoietic systems; (v) presence of serious digestive system diseases, such as peptic ulcer, upper gastrointestinal bleeding, gastric tumor, Crohn's disease, irritable bowel syndrome, etc.; and (vi) participation in other clinical trials within the last three months.

### Recruitment procedures

BC patients in emergency department of the First People's Hospital of Longquanyi District (West China Longquan Hospital Sichuan University) will be diagnosed by emergency physician. Simultaneously, researchers will be responsible for the screening and presenting the inclusion criterion, the operational and allocated details of intervention (acupuncture group and sham acupuncture group), and the potential risks of this trial. All subjects will have the right to withdraw from the trial at any time. Additionally, all subjects will be required to sign an informed consent form before the trial commences.

### Randomization and allocation

Baseline evaluation will be conducted for eligible subjects. The random sequence will be generated using SAS® 9.4 software (SAS Institute Inc., North Carolina, USA). The random sequence will be recorded on sealed and opaque envelopes, with the random numbers of the two groups inside. Moreover, these envelopes will be opened sequentially by a researcher assistant who is not involved in the data collection or acupuncture treatment. In addition, the researcher assistant will randomly assign the subjects to the acupuncture group and the sham acupuncture group with ratio of 1:1.

### Blinding

The researcher assistants, outcome assessors, statisticians and subjects will be blinded to the group assignment. All subjects will receive acupuncture treatment lying on the bed in a quiet clinic. The control group will use a non-penetrating sham apparatus, similar in appearance to acupuncture needles, to achieve blinding. Furthermore, all subjects will be asked about their experience after the acupuncture session to assess whether they have been successfully blinded.

### Interventions

#### Acupuncture group

Yanglingquan (GB34) is acupoint of the gallbladder meridian of foot-shaoyang (GB), which is frequently used for Biliary disease [28, 29]. Therefore, right GB34 will be chosen as the acupuncture point to treat BC. Acupuncture treatment will be performed by acupuncturists with more than 3 years of clinical experience. The acupuncturist will disinfect the skin around the right GB34 with a 70% isopropyl alcohol swab when the subjects lie on the treatment bed in a supine position. Disposable sterile acupuncture needles (0.25 mm in diameter and 40 mm in length, Hwatuo, Suzhou, China) will then be inserted in the right GB34 (Fig. 2B). The needle will be lifted and thrust approximately 30–50 mm and twisted and rotated approximately 90° to 180° angle for 60–90 times/min to achieve deqi sensation, including soreness, numbness, heaviness, fullness, and aching. The deqi sensation will be evaluated using the Chinese version of the modified Massachusetts General Hospital Acupuncture Sensation Scale (C-MASS). All subjects will receive one 30-min acupuncture treatment during their waiting time after routine examination, and the manipulations will be executed two times, once every 10 min, for 60 s each time.

**Fig. 2 Fig2:**
[figure not shown]
The diagram of acupuncture and non-penetrating sham apparatus

#### Sham acupuncture group

The right non-acupuncture point located at the lateral edge of the tibia, approximately 1–2 cm away from Zusanli (ST36), will be selected as the sham point [30]. A non-penetrating sham apparatus with a blunt tip, specifically the Park sham device, will be used to lightly touch the skin at the sham point [31] (Fig. 2A). The procedures and manipulations in the non-acupuncture group will be identical to those in the acupuncture group. Subjects will receive treatment alone in a single room to prevent any interference from family members or other individuals.

### Outcome measures

#### Primary outcome measures

The primary endpoint is the change of pain intensity from baseline to 30 min after acupuncture by evaluating the NRS. The NRS is a 10-point scale, with zero representing "no pain" and 10 representing "worst possible pain". The pain intensity of BC subjects will be presented by marking a “√” on the line of NRS.

#### Secondary outcome measures

The secondary end points will be evaluated as following:

i)The pain intensity will be assessed the change of NRS score from baseline to the 10 min, 20 min and 40 min after needle manipulation.ii)The degree of gastrointestinal symptoms, such as nausea, vomiting and pantothenic acid, will be evaluated for change from baseline by the visual analogue scale (VAS) at 10 min, 20 min, 30 min and 40 min after needle manipulation [32].iii)The level of anxiety during episodes of pain will be measured by changes in the VAS at 10 min, 20 min and 30 min after needle manipulation, compared to baseline [33]. The VAS will be used to assess the anxiety level of patients with BC during pain attacks.iv)The pain-related emotional responses, such as anxiety and fear, will be assessed using the Pain Anxiety Symptoms Scale-20 (PASS-20), the Fear of Pain Questionnaire-III (FPQ-III), and the Pain Catastrophizing Scale (PCS) at baseline [34–37]. The PASS-20 will be used to evaluate whether patients with biliary colic experience anxiety during the non-pain periods.v)The patients' anticipated responses to acupuncture will be evaluated using the Acupuncture Expectancy Scale (AES) at baseline [38].vi)The patient’s satisfaction for acupuncture will be monitored by the 5-point Likert scale at 30 min after needle manipulation [39].vii)The evaluation of needle sensation will be conducted using the Chinese version of the modified Massachusetts General Hospital Acupuncture Sensation Scale (C-MASS) at 10 min, 20 min and 30 min after needle manipulation [40].viii)The use of rescue analgesia will be recorded 10 min after the completion of acupuncture. The recurrence rate of BC and any adverse events occurring within 72 h after needle manipulation will be obtained through a telephone follow-up.

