### Statistical analysis

The independent samples t-test or Wilcoxon rank-sum test will be used to analyze continuous variables in the demographic characteristics of the two groups, based on their normality. Categorical variables in the demographic characteristics will be analyzed using chi-squared or Fisher's exact tests. If there is a significant difference in demographic characteristics such as age, gender, and family history, they will be included as covariates in the efficacy analysis. The analysis will include all randomized BC patients based on the intention-to-treat (ITT) principle. Subgroup and sensitivity analyses may also be performed.

The change of pain intensity from baseline to 30 min after acupuncture will be analyzed by using analysis of covariance with acupuncture group and sham acupuncture treatment as factors and baseline pain intensity as a covariate. Repeated measures ANOVA will be used to assess the difference in the secondary outcomes at different time points. The degree of patients’ expectations and satisfaction with acupuncture will be evaluated using linear regression.

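### Gastrointestinal endpoint (ii): a change score with no stated baseline adjustment, in patients who may start at zero, dilutes relief, and one named symptom cannot be rated

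*Protocol article*

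**What the plan says.** Under Secondary outcome measures, item (ii) states: "The degree of gastrointestinal symptoms, such as nausea, vomiting and pantothenic acid, will be evaluated for change from baseline". The instrument is a VAS, read at 10, 20, 30 and 40 min after needle manipulation. The abstract describes the endpoint only as "the degree of gastrointestinal symptoms at different time points".

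The only symptom score required by the Inclusion criteria is for pain: "a numerical rating scale (NRS) score of ≥ 3 points". No criterion asks for nausea, vomiting or any other gastrointestinal symptom. The Background does treat them as part of the condition, describing pain "as well as nausea and vomiting, which are caused by the contraction of the gallbladder pushing bile across the blockage", but gives no frequency.

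Under Statistical analysis: "The analysis will include all randomized BC patients based on the intention-to-treat (ITT) principle". The primary outcome gets an analysis of covariance with baseline pain as covariate. For the rest, "Repeated measures ANOVA will be used to assess the difference in the secondary outcomes at different time points", with no baseline symptom score named as covariate. Demographic variables enter the efficacy analysis only if they differ significantly between arms.

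**The concern.** Two things look wrong.

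First, the pain criterion leaves every patient room to improve on the primary outcome. Nothing comparable holds for the gastrointestinal VAS. A patient who enters without nausea sits at the floor of the scale and cannot show relief, yet contributes a change score to the mean. The more such patients there are, the smaller the average difference between arms. An unadjusted change score also carries the spread between patients who could improve and patients who could not. A baseline covariate removes most of that spread, and the article names one only for the primary outcome.

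Second, pantothenic acid is a vitamin. A patient cannot rate its degree, and nothing else in the article shows which symptom was meant.

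At stake is the trial's only measure of gastrointestinal symptoms, in a study whose stated aim includes relief of symptoms associated with the pain. A true benefit could be missed or reported as smaller than it is in the patients who have the symptom.

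**Working it through.** The article states no figure for this endpoint, so there is none to reproduce. The check asks how much the floor costs and how much a baseline covariate recovers.

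**Inputs from the article.** 76 evaluable patients (Sample size calculation) and 1:1 allocation give 76/2 = 38 per arm; two-sided 5%.

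**Assumed inputs, not in the article.** A share s of patients is symptomatic at baseline; the others have a change of 0. Among symptomatic patients the SD of change is 1, mean improvement is 0.5 on sham and 0.5 + e on acupuncture, with e = 0.83 or 0.5 SD.

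**Dilution of the mean.** Difference over all patients = s × e. For illustration, an assumed relief of 20 mm in symptomatic patients becomes 0.40 × 20 = 8 mm or 0.70 × 20 = 14 mm. That is a loss of 60% or 30% in the mean. It is not the loss of power, because patients fixed at 0 also reduce the variance.

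**Power formula.** Power = Φ(difference/SD × √(38/2) − 1.96), with √19 = 4.359.

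- *Unadjusted:* variance = s + s(1−s) × average of m² over the arms. For e = 0.83, m is 0.5 and 1.33, so the average is (0.25 + 1.769)/2 = 1.009.
- *Baseline-adjusted, all patients:* in its simplest form the covariate separates patients at 0 from the others. The common slope absorbs the average improvement, and ±e/2 is left in each arm. Variance = s + s(1−s)(e/2)².
- *Symptomatic patients only:* difference e, SD 1, 38s per arm.

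**Worked case, s = 0.6, e = 0.83.** Difference = 0.498.

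- Unadjusted: variance 0.6 + 0.24 × 1.009 = 0.842, SD 0.918; 0.498/0.918 × 4.359 = 2.365; Φ(0.405) = 66%.
- Adjusted: variance 0.6 + 0.24 × 0.172 = 0.641, SD 0.801; 0.498/0.801 × 4.359 = 2.71; Φ(0.75) = 77%.
- Symptomatic only: 0.83 × √(22.8/2) = 2.80; Φ(0.84) = 80%.

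| Share symptomatic | e = 0.83: unadjusted / adjusted / symptomatic only | e = 0.5: unadjusted / adjusted / symptomatic only |
|---|---|---|
| 100% | 95 / 95 / 95% | 59 / 59 / 59% |
| 80% | 84 / 89 / 90% | 45 / 49 / 50% |
| 60% | 66 / 77 / 80% | 33 / 38 / 39% |
| 40% | 44 / 59 / 63% | 22 / 27 / 28% |
| 20% | 23 / 33 / 37% | 12 / 16 / 16% |

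Simulating the same model with t-tests at e = 0.83 and shares of 80%, 60% and 40% agreed with the unadjusted and adjusted columns to within about 2 points. A separate simulation on other assumed inputs, also with 38 per arm, moved the same way: from about 65% to 82% with 70% symptomatic and from 35% to 56% with 40%. There, adjustment matched the symptomatic-only analysis.

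So adjustment recovers most or all of what restriction to symptomatic patients would gain, and it keeps the randomized set whole.

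**The wrong term.** No arithmetic applies. Nausea and vomiting appear in both the Background and item (ii); pantothenic acid appears only in item (ii), with nothing to interpret it by.

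**The case against.** The strongest reply is that most of this is ordinary. Symptom-free patients are expected equally in both randomized arms, so the floor dilutes the comparison but does not bias it. Analysing everyone follows the stated ITT principle and also counts new-onset symptoms. Because the Background calls nausea and vomiting characteristic, many patients may start above 0. Scoring details and the handling of zero baselines may sit in a full protocol or analysis plan that is not shown. The symptom list is open-ended, the odd word is probably a translation slip, and the case report form may have it right. The sample size does not rest on this endpoint.

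Most of that stands, and it keeps the point minor. It does not remove it: the article itself fixes change from baseline in all randomized patients, names the method for secondary outcomes, and attaches a baseline covariate to the primary outcome alone.

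A reader might go further in three ways that the article does not support.

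- *That the endpoint cannot show relief.* Dilution is not inability: at an effect of 0.83 SD, unadjusted power is still 84% with 80% symptomatic.
- *That vomiting between readings will be missed.* This assumes a momentary rating. The text gives no recall period, and a rating could cover the preceding 10 min. A VAS is a weak fit for an episodic event, but using one is not an error.
- *That the main analysis should be limited to symptomatic patients.* This departs from the stated ITT set and, at 40% symptomatic, leaves about 0.4 × 38 = 15 per arm. The working shows little or no gain over adjustment.

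**Conclusion.** The point holds as a minor one. As the article describes it, endpoint (ii) averages change over patients who may have nothing to relieve and states no baseline adjustment, so it understates relief and loses power. The loss depends on the share symptomatic at baseline, which is not given. Under the assumptions above, adjustment would add about 12 points of power at 60% symptomatic (66% to 77% as rounded) and 15 at 40% (44% to 59%) if the effect is 0.83 SD, but only about 5 to 6 points at those shares if it is 0.5 SD. It would add nothing if everyone is symptomatic. The effect sizes, the sham improvement and the shares are all assumptions, so these figures show direction and rough scale only.

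The error in the symptom name is certain; its consequence is small if it is only a slip in the article.

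**What to change.** - Analyse each symptom's VAS change in all randomized patients, with that symptom's own baseline VAS as covariate. The baseline score is already collected, so this costs nothing in data.
- As supportive analyses, report relief among patients with a baseline score above 0, and new onset by arm among those starting at 0. Both subsets are fixed before treatment; label the results exploratory.
- Preferably record vomiting as the number of episodes up to 40 min. If the VAS is kept, state its recall period.
- Have the investigators replace pantothenic acid with the symptom they meant. Acid regurgitation is a plausible guess, but only they can confirm it.

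The cost is some protocol and case report form wording and a little more analysis, with no added visit or staff. The article's Trial status section says that no subject had yet been recruited, so at that stage the forms could change without loss of data. The downside is a few more results from one secondary outcome, which is why the supportive ones should not carry confirmatory claims.
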